#### Preliminary findings

We conducted a feasibility study using OSA screening tools among blacks at the community level to provide (1) estimates of the likely rates of OSA in the community, which will in turn guide our recruitment strategies, (2) an empirical basis for our sample size calculations, and (3) preliminary evidence that education and support offered by a peer health educator led to OSA evaluation among blacks at risk.

Over a 15-day period, we randomly assigned 27 blacks to an intervention group (peer health educator) and 25 to a control group (publicly available sleep brochures and literature). The desired behavior was limited to ‘making an appointment for an OSA assessment’. Analysis showed that 26% of blacks in the control condition made an appointment for OSA assessment, whereas 41% of those exposed to the intervention arm made an appointment. Although results were in the expected direction, we were unable to determine whether participants would show up for OSA assessment and/or adhere to treatment. This requires long-term monitoring and justifies the purpose of our study.

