#### Sample size and power analysis

We plan to screen approximately 1250 blacks in the community. Assuming 39% of blacks are at risk for OSA, we propose to enroll 398 men and women (199 per study arm). With a 35% attrition rate, 258 will have provided adherence data during 6-month follow-up assessment. Based on the pilot data, we expect that 41% in the intervention arm (*n* = 82) and 26% in the attention-control arm (*n* = 52) will have completed all aspects of the trial, including site interview, home evaluation, and follow-up assessment (Fig. 2).

The primary study outcome is receipt of home OSA evaluation after tailored peer-based sleep health education. Data obtained from a sample of blacks provided a current estimate of the likely OSA evaluation rate we expect in the partner community. Analysis showed that 41% of participants adhered to recommended OSA evaluation after intervention exposure, whereas 26% of participants in a control group agreed to undergo evaluation. These preliminary findings represent the likely adherence rates expected in our proposed study.

We propose to achieve an evaluation rate in our intervention arm of 41% based our pilot study mentioned above. This would represent a 63% greater adherence rate compared with controls, which potentially would have a significant public health impact. Assuming a 15% increase in the likelihood of undergoing home-based OSA evaluation, a standard error of 0.09% and a sample size of 398, the study will be adequately powered (> 85%) to detect a significant increase in adherence. Specifically, an observed difference of 15% would be reported with a 95% CI 7–24%. A two-tailed test, with 80% power and α = 0.035 comparing adherence rates of 26% with 41% requires 199 participants per group. Of note, our sample size estimate adjusted for potential intra-cluster coefficient that may be observed in both the treatment and control arms, which according to our initial pilot was 0.014. The resulting effective sample size (*ESS = [M x K/DE]*) after adjustment for design effect (*DE*)… [*DE = 1 + (n-1)ρ*] was *n* = 398 (199 participants per arm) [97, 98]. The study is also powered to assess differences in adherence rates to CPAP treatment between the two arms considering the likely attrition rate of 35% during follow-up assessment.

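### The 26% pilot control rate used for sizing does not fit the 25 controls assigned, and the stated relative increase, standard error and confidence interval do not follow from the plan's own rates

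*Protocol article*

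**What the plan says.** Preliminary findings presents the feasibility pilot as, among other things, "an empirical basis for our sample size calculations". On its size: "we randomly assigned 27 blacks to an intervention group (peer health educator) and 25 to a control group". On its result: "Analysis showed that 26% of blacks in the control condition made an appointment for OSA assessment, whereas 41% of those exposed to the intervention arm" did so. The section gives percentages only. It reports no counts and does not say whether every assigned participant had an outcome.

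Sample size and power analysis adopts both percentages as the rates expected in the trial. The intervention rate is tied to the pilot: "We propose to achieve an evaluation rate in our intervention arm of 41% based our pilot study mentioned above". The control rate of 26% is presented as coming from the same data. The section then states:

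- the relative effect: "This would represent a 63% greater adherence rate compared with controls";
- the power: "a sample size of 398, the study will be adequately powered (> 85%) to detect a significant increase in adherence", with a standard error given as 0.09%;
- the precision: "an observed difference of 15% would be reported with a 95% CI 7–24" (per cent);
- the sample size: "A two-tailed test, with 80% power and α = 0.035 comparing adherence rates of 26% with 41% requires 199 participants per group".

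**The concern.** The control rate fixes the size of the effect to be detected, and so the power. Here it is attributed to a group of 25 in which it cannot occur if all 25 were counted. The companion figure does fit its group (11/27 is 40.7%), so rounding does not explain the mismatch. A reader cannot tell whether the pilot lost controls, whether a denominator was misapplied, or whether the percentage is a slip.

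This matters because the claim of more than 85% power has almost no slack at 26%. A control rate two points higher would take the trial below both powers the section states. Two points lower would leave it comfortably above them.

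The relative increase and the precision statement raise a separate question. They should follow from 26%, 41% and 199 per arm by simple arithmetic, wherever the 26% came from.

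**Working it through.** **Inputs.** Pilot groups of 27 and 25, and rates of 41% and 26% (Preliminary findings). Planning rates of 41% and 26%, two-sided alpha 0.035, 199 per arm (Sample size and power analysis).

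**1. Can 26% arise from the pilot?**
- Out of 25: 6/25 = 24.0%, 7/25 = 28.0%. Nothing lies between.
- Out of 27: 11/27 = 40.7%, which matches the reported 41%; 7/27 = 25.9%, which rounds to 26%.
- Of denominators from 15 to 25, only 19 and 23 can give 26% after rounding (5/19 = 26.3%, 6/23 = 26.1%). The smaller loss is two controls without an outcome.

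**2. Reproducing the stated power.** Normal approximation for two proportions, pooled variance under the null, no clustering or attrition. The average rate is 0.335 and z for alpha 0.035 is 2.108.
- Null standard error: √(2 × 0.335 × 0.665 / 199) = 0.0473
- Alternative standard error: √((0.26 × 0.74 + 0.41 × 0.59) / 199) = 0.0467
- Power = Φ((0.15 − 2.108 × 0.0473) / 0.0467) = Φ(1.075) = 85.9%

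So the stated power reproduces from the planning rates.

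**3. Sensitivity to the control rate.** Intervention 41%, 199 per arm, same method:

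| Control rate | Difference (points) | Relative increase | Power, alpha 0.035 | Power, alpha 0.05 | n per arm for 80% power, alpha 0.035 |
|---|---|---|---|---|---|
| 24% (6/25) | 17 | 71% | 93.8% | 95.4% | 131 |
| 26% (as stated) | 15 | 58% | 85.9% | 89.0% | 172 |
| 28% (7/25) | 13 | 46% | 73.4% | 78.1% | 232 |

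The sample sizes are rounded up and exclude any design effect. The plan says its 199 includes an adjustment for clustering, so 172 is not in itself a contradiction.

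**4. Relative increase.** 41/26 = 1.577, or 58% greater. To obtain 63%, the control rate would have to be 41/1.63 = 25.2%. Neither 24% nor 28% gives it.

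**5. Standard error and interval.**
- At 199 per arm the standard error is 0.0467, or 4.7 percentage points.
- The 95% interval is 15 ± 1.96 × 4.67 = 5.8% to 24.2%.
- The printed limits of 7% and 24% lie 8 points below and 9 points above 15%, so they are not symmetric.
- A standard error of 0.09 percentage points would give about 14.8% to 15.2%.
- Read as 9 percentage points, it would give 15 ± 17.6, or about −3% to 33%.
- Neither reading yields the printed interval. The correct half-width is 9.2 points, so 0.09 may be a half-width entered as a standard error; the article does not say.

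**The case against.** The article says 25 were assigned to control, not that 25 were analysed. Over a short community pilot, two controls without an outcome would be unremarkable, and 6/23 rounds to 26%. This stands: 26% is inconsistent with the stated group only if all 25 were counted. It does not remove the need to disclose the denominator.

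A planning rate is also an assumption, and the power is correctly computed from it. The section on assessment and treatment barriers separately cites 26% adherence in a previous study, so the value is not arbitrary. This too stands, although the sizing section takes its rates from the pilot, not from that study.

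The mismatch is small beside the pilot's own imprecision. Exact 95% intervals run from about 9% to 45% for 6/25 and from 12% to 49% for 7/25. Attrition weighs more as well. With the 258 participants expected to provide data (129 per arm), 26% against 41% has about 67% power at alpha 0.035, if those lost are left out of the analysis. Both points limit how much turns on the 26%, but neither makes it consistent with its stated source.

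A reader might go further and infer that the trial is underpowered because its control rate is impossible. The article does not support that. If the count was 7/25, power falls; if 6/25, it rises; if the true fraction was 6/23 or 7/27, it is essentially unchanged. Nor does the 63% figure rest on the 26% rate: 26% gives 58%, so that is an independent slip on which no power or sample size figure depends.

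**Conclusion.** The point holds as a discrepancy in reporting and arithmetic within the sizing justification. The stated power is not shown to be wrong.

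- The control rate does not match the 25 controls to whom it is attributed, unless some were left out or another denominator was used. The article states neither.
- Power above 85% reproduces by less than one point at alpha 0.035, before clustering and attrition. It ranges from 73.4% to 93.8% over the two whole-count rates nearest to 26%. These figures assume 41% in the intervention arm, 199 independent and fully observed participants per arm, and the normal approximation.
- On the plan's own rates, the relative increase should be 58%, the standard error 4.7 percentage points, and the 95% interval about 6% to 24%. These three corrections do not depend on how the pilot question is resolved, as long as 26% and 41% remain the planning rates. The interval's lower limit moves by only about one point; the standard error is wrong by a factor of about fifty (4.67/0.09).

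**What to change.** In Preliminary findings, give the pilot result for each arm as a count over the number analysed, and mention any participant without an outcome. If the control denominator was 23 or 27 rather than 25, say so and explain why.

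In Sample size and power analysis, if the counts do not give 26%, restate the planning rate and the power at alpha 0.035 with 199 per arm: about 94% for 6/25 and about 73% for 7/25, before clustering and attrition. If 26% is kept as an assumption, say that it is one and what supports it.

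In the same section, change the relative increase to 58%, the standard error to 4.7 percentage points and the interval to about 6% to 24%. If the planning rate changes, recompute all three from the new rate.

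The cost is a look-up of the pilot records and a few corrected sentences. Enrolment, design and analysis do not change. The restated power may turn out less favourable than the one now printed.

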#### Sample size and power analysis

We plan to screen approximately 1250 blacks in the community. Assuming 39% of blacks are at risk for OSA, we propose to enroll 398 men and women (199 per study arm). With a 35% attrition rate, 258 will have provided adherence data during 6-month follow-up assessment. Based on the pilot data, we expect that 41% in the intervention arm (*n* = 82) and 26% in the attention-control arm (*n* = 52) will have completed all aspects of the trial, including site interview, home evaluation, and follow-up assessment (Fig. 2).

The primary study outcome is receipt of home OSA evaluation after tailored peer-based sleep health education. Data obtained from a sample of blacks provided a current estimate of the likely OSA evaluation rate we expect in the partner community. Analysis showed that 41% of participants adhered to recommended OSA evaluation after intervention exposure, whereas 26% of participants in a control group agreed to undergo evaluation. These preliminary findings represent the likely adherence rates expected in our proposed study.

We propose to achieve an evaluation rate in our intervention arm of 41% based our pilot study mentioned above. This would represent a 63% greater adherence rate compared with controls, which potentially would have a significant public health impact. Assuming a 15% increase in the likelihood of undergoing home-based OSA evaluation, a standard error of 0.09% and a sample size of 398, the study will be adequately powered (> 85%) to detect a significant increase in adherence. Specifically, an observed difference of 15% would be reported with a 95% CI 7–24%. A two-tailed test, with 80% power and α = 0.035 comparing adherence rates of 26% with 41% requires 199 participants per group. Of note, our sample size estimate adjusted for potential intra-cluster coefficient that may be observed in both the treatment and control arms, which according to our initial pilot was 0.014. The resulting effective sample size (*ESS = [M x K/DE]*) after adjustment for design effect (*DE*)… [*DE = 1 + (n-1)ρ*] was *n* = 398 (199 participants per arm) [97, 98]. The study is also powered to assess differences in adherence rates to CPAP treatment between the two arms considering the likely attrition rate of 35% during follow-up assessment.

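### The standard error of 0.09% in the power calculation cannot be right (the plan's own rates and numbers give 4.7 percentage points), and the lower limit of the 95% CI of 7–24% is about one point too high

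*Protocol article*

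**What the plan says.** In the protocol article, the section on sample size and power analysis expects 26% of controls and 41% of the intervention arm to undergo home OSA evaluation, with 398 participants enrolled, 199 per arm. The power statement begins "Assuming a 15% increase in the likelihood of undergoing home-based OSA evaluation", and the variability input and the power claimed from it read "a standard error of 0.09% and a sample size of 398, the study will be adequately powered (> 85%) to detect a significant increase in" the evaluation rate. The next sentence states the precision to be expected: "an observed difference of 15% would be reported with a 95% CI 7–24" (per cent). A separate sentence gives a second calculation: "A two-tailed test, with 80% power and α = 0.035 comparing adherence rates of 26% with 41% requires 199 participants per group". The section also says that the sample size was adjusted for an intra-cluster coefficient of 0.014 and that the effective size after adjustment is 398.

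**The concern.** For two proportions, the standard error of the difference follows from the rates and the numbers per arm, and the plan states both. A standard error of 0.09% is far too small for about 200 people per arm. It also conflicts with the interval in the next sentence, because a 17-point-wide interval cannot come from a standard error of a tenth of a point.

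These are the only figures in the article on how precisely the primary effect will be estimated, and the standard error is offered as an input to the power claim. A reader who tries to check the calculation from the printed inputs will fail. The lower confidence limit for the planned effect is also shown as slightly better than the design delivers.

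**Working it through.** Inputs, all from the section on sample size and power analysis: rates 0.41 and 0.26, difference 0.15, n = 199 per arm, printed SE 0.09%, printed 95% CI 7–24%, claimed power above 85%, and α = 0.035 two-tailed in the separate calculation. I also show α = 0.05, because the power sentence names no level.

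**1. Standard error from the design.**
SE = √(0.41×0.59/199 + 0.26×0.74/199) = √(0.4343/199) = 0.0467, or 4.67 percentage points.
The pooled form gives 0.0473. With 198 per arm, the figure in the methods and design section, the SE is 0.0468.
Ratio to the printed value: 4.67/0.09 ≈ 52.
Number per arm needed for an SE of 0.09%: 0.4343/0.0009² ≈ 536,000.

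**2. Can the printed SE give the printed interval or power?** The interval is 0.15 ± 1.96×SE and power is Φ(0.15/SE − z), with z = 1.96 at α = 0.05 and 2.108 at α = 0.035.

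| SE used | 95% CI | Power, α = 0.05 | Power, α = 0.035 |
|---|---|---|---|
| 0.09% as printed | 14.8% to 15.2% | about 100% | about 100% |
| 9 points (percent sign taken as a slip) | −2.6% to 32.6% | about 38% | about 33% |
| 4.67 points (design) | 5.8% to 24.2% | about 89% | about 86% |

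Neither reading of the printed value gives 7–24%. The literal reading exceeds 85% power only in the trivial sense that power would be complete; the 9-point reading falls far short. The last row uses the pooled SE under the null hypothesis (0.890 and 0.859). The simple formula with 0.0467 gives 0.89 and 0.87.

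**3. Can the design give the printed interval?**
- Wald: 15 ± 1.96×4.67 = 15 ± 9.2, so 5.8% to 24.2%.
- Newcombe, on the plan's expected counts of 82/199 and 52/199: 5.8% to 24.0%.
- Wald with continuity correction: 5.3% to 24.7%.
- With a design effect 1 + (m − 1)×0.014 applied to 199 per arm, where the cluster size m is my assumption because the article gives none: lower limit 5.8% at m = 2, falling to 4.1% at m = 30.

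None of these gives a lower limit of 7%.

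**4. What the printed interval would imply.** Its width gives SE = 17/(2×1.96) = 4.34 points, which needs 0.4343/0.0434² ≈ 231 per arm. A symmetric interval with a lower limit of 7% has a half-width of 8 points, so SE = 8/1.96 = 4.08 points and about 261 per arm.

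**5. A possible origin.** The 95% half-width is 1.96×0.0467 = 0.092. Rounded to 0.09, labelled a standard error and given a percent sign, it would be the printed figure. This is inference; the article does not say how the number arose.

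**The case against.** The best defence is that the wrong number drives nothing. Power above 85% reproduces from the stated rates and 199 per arm, the sample size does not change, and the interval is off by about a point at one end only. That stands, and it limits the point to a correction of printed figures. It does not make the standard error right, nor does it reconcile it with the sentence that follows. Nor is this a detail that a condensed article leaves to a fuller document: the wrong figure is stated outright.

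Four stronger readings are tempting, and the documents do not support them.

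- *A positive trial would be taken to exclude effects below 7 points.* The interval is given only for an observed difference of 15%. With an SE of 4.67 points, an observed difference just above 1.96×4.67 = 9.2 points would already be significant at 0.05, with a lower limit near zero. The article claims nothing about other results.
- *The interval is wrong because it is not centred on 15%.* Asymmetry is not in itself an error. Score-type intervals are asymmetric too, and rounding plays a part.
- *The precision should be computed on 258 people.* The plan does say "With a 35% attrition rate, 258 will have provided adherence data during 6-month follow-up assessment". But its expected counts of 82 and 52 are 41% and 26% of 199, the analysis is by intention to treat, and the home-study outcome is a yes or no on whether the person took part. Whether attrition reduces the numbers for the primary outcome is a separate question.
- *The interval should be at a level matching α = 0.035.* Reporting a 95% interval beside another test level is a matter of preference, and the analysis sections do not fix 0.035 as the reporting level.

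**Conclusion.** The point holds as a correction of two printed figures of very different weight. The standard error is wrong by a factor of about 52 (0.09% against 4.67 percentage points), and no reading of it yields the printed interval. The 95% CI is right at its upper limit and about one point optimistic at its lower limit (7% against 5.8%).

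The recomputed values assume the stated rates, 199 participants per arm with a known outcome, and independent observations. The last assumption can be taken from the plan's statement that 398 is the effective size after adjustment for clustering; whether that adjustment is sound is not examined here. A reader might infer that the power claim or the sample size of 398 falls with the standard error. Neither does: with 199 per arm the power is about 86% to 89%.

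**What to change.** In the section on sample size and power analysis:

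- Replace the standard error of 0.09% with a standard error of the difference of 4.7 percentage points.
- Replace the 95% CI of 7–24% with a 95% CI of about 6–24%.
- Add that both figures assume outcome data on an effective 199 participants per arm.

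The cost is one corrected sentence pair. Enrolment, procedures, analysis and the power claim at 199 per arm stay as they are; the stated precision becomes slightly less favourable.

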## Methods and design

In a two-arm, randomized controlled trial, we will ascertain effectiveness of peer-based sleep health education and social support in increasing OSA evaluation and treatment rates among 398 blacks at risk for OSA (198 participants in treatment group and 198 participants in attention-control group), over a 12 month period. Participants in the intervention arm will receive quality-controlled, culturally, and linguistically tailored peer education using a sleep health education manual developed based on principles of motivational enhancement. Participants in the treatment arm will each receive up to five peer-based sessions promoting OSA evaluation. Those with an OSA diagnosis will receive five additional peer-based sessions promoting OSA treatment compliance and adherence from a peer health educator contingent upon poor treatment adherence from CPAP-based reports. Those in the attention-control arm will receive standard OSA literature from the study staff. Regardless of group assignment, we will ascertain all outcomes at baseline and at 6- and 12-month follow-up assessments.

The study was approved by the New York University Langone Health Institutional Review Board and all participants will be consented by study staff before enrollment. The trial is in accordance to the Consolidated Standards of Reporting Trials (CONSORT) Statement on randomized trials for non-pharmacological treatment and the Standard Protocol Items: Recommendations for Interventional Trials SPIRIT checklist (see Additional file 1 for CONSORT Figure, SPIRIT Figure and checklist Figs. 2 and 3) [37, 38].

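### The power statement contradicts itself: above 85% and 80% for the same 199 per arm, an effective sample size equal to enrolment, no allowance for the stated 35% attrition, and wrong precision figures

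*Protocol article*

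**What the plan says.** All but one of these statements come from the protocol article, section Sample size and power analysis, and concern receipt of a home OSA evaluation, the primary outcome, at 41% against 26%.

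- First power figure, put at above 85% with no alpha attached: "a sample size of 398, the study will be adequately powered".
- Second power figure, for the same rates: "A two-tailed test, with 80% power and α = 0.035", "comparing adherence rates of 26% with 41% requires 199 participants per group".
- Attrition: "With a 35% attrition rate, 258 will have provided adherence data during 6-month follow-up assessment".
- Precision: a standard error of 0.09%, and "an observed difference of 15% would be reported with a 95% CI" of 7 to 24%.
- Relative effect: "This would represent a 63% greater adherence rate compared with controls".
- Clustering: the size is said to be adjusted for an intra-cluster coefficient of 0.014, and the effective sample size after the design effect is given as 398. No cluster size is given.

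The section Methods and design gives the arms as "198 participants in treatment group and 198 participants in attention-control group", which adds to 396, beside a total of 398.

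**The concern.** One design cannot have both powers unless something differs between the two statements, and the section does not say what differs. The planned primary analysis is a GEE chosen because it handles clustering, so a power that ignores clustering does not describe it. The effective sample size as reported implies that clustering costs nothing, which the stated coefficient rules out. The attrition figure stands in the same section but enters neither power statement.

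This is the sample size justification for the primary outcome. The Limitations section also makes the choice between GEE and a fallback analysis depend on reaching an adequate sample size. That condition is hard to judge while the section supports two different powers. A null result would also be read against whichever power figure the reader happens to take.

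**Working it through.** **Inputs.** Rates 0.26 and 0.41, 199 per arm, two-sided alpha 0.035, ICC 0.014 and 35% attrition, all from the sample size section. Alpha 0.05 is an assumption, implied only by the 95% confidence interval. Cluster size *m* is an assumption; the training section gives only a concurrent case load of 3–4 per educator.

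**Formula.** With mean rate 0.335, power = Φ[(0.15 − z·√(0.44555/n)) / √(0.4343/n)], where 0.44555 = 2 × 0.335 × 0.665 and 0.4343 = 0.26 × 0.74 + 0.41 × 0.59. For clustering, n is divided by DE = 1 + (m − 1) × 0.014.

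**Reproducing the first figure.** With n = 199 the two standard errors are 0.0473 and 0.0467.
- Alpha 0.035 (z = 2.108): (0.15 − 0.0998)/0.0467 = 1.075, power 85.9%.
- Alpha 0.05 (z = 1.960): 1.226, power 89.0%.

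So above 85% reproduces for 398 independent participants without losses. With a continuity correction the values are 83.3% and 86.8%.

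**Reproducing the second figure.** 80% power at alpha 0.035 needs 172 per arm without clustering (185 with a continuity correction). To reach 199 requires DE = 199/172 = 1.157, or m = 1 + 0.157/0.014 ≈ 12. With the continuity correction it requires DE = 199/185 = 1.076, or m ≈ 6. The second figure therefore appears to include clustering, but the design effect can only be guessed.

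**Power by number analysed and assumed cluster size.** The 35% attrition leaves 398 × 0.65 = 258.7; the section gives 258, or 129 per arm.

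| Analysed per arm | m | alpha 0.035 | alpha 0.05 |
|---|---|---|---|
| 199 | 1 | 85.9% | 89.0% |
| 199 | 3 | 84.9% | 88.1% |
| 199 | 4 | 84.4% | 87.7% |
| 199 | 10 | 81.3% | 85.1% |
| 199 | 20 | 76.4% | 80.7% |
| 129 | 1 | 67.4% | 72.6% |
| 129 | 4 | 65.4% | 70.8% |
| 129 | 10 | 61.8% | 67.4% |
| 129 | 20 | 56.4% | 62.3% |

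Inflating for 35% loss would give 172/0.65 = 265 per arm at alpha 0.035 or 155/0.65 = 239 at alpha 0.05, so 199 contains no attrition allowance.

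**Effective sample size.** It equals 398/DE, which is 398 only if DE = 1. At m = 4 it is 398/1.042 = 382; at m = 10 it is 398/1.126 = 353.

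**Precision and effect.**
- Standard error of the difference: √(0.4343/199) = 0.0467, or 4.7 percentage points, against a stated 0.09%.
- 95% CI: 15 ± 1.96 × 4.67 = 5.8 to 24.2%, against 7 to 24%. Rounding could explain a midpoint of 15.5, but 5.8 does not round to 7. The stated width implies a standard error of (24 − 7)/(2 × 1.96) = 4.3 points.
- Relative increase: 0.41/0.26 = 1.577, or 58%, against 63%.
- Arms: 198 + 198 = 396, against 398.

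**The case against.** The best defence has three parts.

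First, the figure above 85% carries no alpha. If it was computed at 0.05, as the 95% interval suggests, it holds with clustering up to about ten per cluster, and it need not conflict with 80% at 0.035. This stands as a possible reconciliation, but the section never makes it.

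Second, attrition may not touch the primary analysis. Research staff carry out the home study, so receipt should be known from study records. The analysis is by intention to treat. The expected 82 and 52 are 41% and 26% of 199, so the rates are applied to everyone enrolled. The 258 is tied to adherence data at six months, and the section links attrition to power only when it turns to CPAP. A reader might infer from the 258 that the stated power is not delivered and that the trial really has about 60–73%. The documents do not support that as a fact: it requires the primary analysis to be limited to the 258, and these features point the other way. The text does not settle it outright, however. If losses instead diluted the rates on 199 per arm (0.65 × 41% = 26.7% and 0.65 × 26% = 16.9%), power would be 60–66%.

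Third, calling 398 the effective sample size may be only a mislabelling of enrolment after inflation. That is the likely explanation, and the label is still wrong. For the same reason, a design effect of about 1.16 is back-solved from an uncorrected formula (about 1.08 with a continuity correction) and should not be entered in the protocol as a known value.

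**Conclusion.** The concern holds as an internal inconsistency with wrong supporting figures. It does not show that the trial is underpowered for its primary outcome.

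At the only stated alpha, above 85% describes 199 essentially independent, fully observed participants per arm; with three per cluster it has already fallen to 84.9%. At alpha 0.05 it is tenable up to about ten per cluster. If all 398 are analysed and the section's own 199-per-group calculation is kept, the power to state is 80% at alpha 0.035. The values of 67% and 73% are conditional on analysing only the 258 and contain no clustering; with clustering they are lower. All clustered values rest on an assumed cluster size.

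The effective sample size, standard error, confidence interval, relative increase and arm sizes are wrong or contradictory whichever reading is taken.

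**What to change.** 1. State that the primary outcome, receipt of the home study, is scored from study records for all 398 randomised, with no home study counted as a no. Attrition then does not shrink the primary analysis. If this is not intended, state a power of at most 67% (alpha 0.035) or 73% (alpha 0.05), less the effect of clustering.
2. Give one alpha, one power, and the cluster size and design effect behind them. If the 199-per-group calculation is kept, that is 80% at alpha 0.035. Drop the figure above 85% unless an alpha and cluster size are stated that support it. Report the effective sample size as 398/DE. Explain alpha 0.035, and make the interval level agree with it or say why it differs.
3. Correct the standard error to about 4.7 percentage points, the 95% CI to about 5.8–24.2% (wider with clustering), 63% to 58%, and 198 to 199 per arm in Methods and design.

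The cost is rewording one section and one number elsewhere. No participants are added; the stated power and precision become slightly less favourable.
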